Trouble falling or staying asleep, or sleeping too much	0	1	2	3
Feeling tired or having little energy	0	1	2	3
Poor appetite or overeating	0	1	2	3
Feeling bad about yourself, or that you are a failure or have let yourself or your family down	0	1	2	3
Trouble concentrating on things, such as reading the newspaper or watching television	0	1	2	3
Moving or speaking so slowly that other people could have noticed? Or the opposite, being so fidgety or restless that you have been moving around a lot more than usual	0	1	2	3
Thoughts that you would be better off dead or of hurting yourself in some way	0	1	2	3
Please could you confirm your answer for this question: Over the last 2 weeks, how often have you been bothered by thoughts that you would be better off dead or of hurting yourself in some way	0	1	2	3
	Total Score ___ = ___ + ___ + ___			
If you checked off any problems, how difficult have these problems made it for you to do your work, take care of things at home, or get along with other people?^a,b^	Not difficult at all	Somewhat difficult	Very difficult	Extremely difficult

^a^General version

^b^Localised version

In keeping with the pragmatic orientation of this trial [57, 58], we intentionally have few exclusion criteria. We only excluded individuals if they planned to move away from the vicinity of the clinic in the next year and would therefore be unable to participate in follow-up data collection, or were otherwise judged unable to provide informed consent because of acute medical illness or psychosis. We did not exclude participants with active suicidal ideation, but urgently referred them for clinical review in both intervention and control arms.

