Viral loads will be measured using venous samples in participants at baseline and at the 12-month follow-up interview, and the samples submitted to the National Health Laboratory Service responsible for routine viral load monitoring, which current ART programme guidelines recommend should occur annually [61]. Thus, the majority of patients are expected to undergo both routine programme and research viral load monitoring during the course of the trial. Funds available for viral load monitoring as part of the trial are limited and therefore only patients with no documented programme results (in the past 6 months) will be asked to submit a baseline research viral load. Research-funded 12-month viral loads will be collected on all patients as this is the primary physical outcome.

We will also aim to collate all programme and research-viral loads into a single longitudinal record for every patient enrolled in the trial, through linkage with the viral load repository at the National Health Laboratory Service and application of algorithms for this linkage previously applied to province-wide ART datasets [27]. In South Africa, detectable viremia is most commonly caused by non-adherence, and only rarely due to resistant virus [62]. Thus, the proportion of participants with a suppressed viral load provides a reasonable estimate of ART adherence. In addition, we have included a Visual Analogue Scale for self-reported adherence in the last month as a secondary outcome measure at 12 months [63–65]. The integrated care nature of the intervention, with a focus on the detection and management of chronic diseases, and the surge in multi-morbidity in the general population, and ART populations in particular [66], are the reasons for monitoring risk factors for cardiovascular diseases (blood pressure, weight, smoking status) and the detection and treatment of other chronic diseases.

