Change in viral load values over time	Viral load values	Research- and programme-funded viral loads	At least half a log difference between viral load values, unless there are two viral loads >2000 copies/ml	●	●	●●
ART treatment	ART regimen	Self-report	Clinically appropriate switches to second line ART therapy	●		●●
ART adherence	Visual Analogue Scale	Self-report	Difference in means	●		●●
Stigma	Internalised AIDS-Related Stigma Scale	Self-report	Difference in means	●		●●
Integrated care outcomes						
Cardiovascular risk factors	blood pressure, weight, body mass index, waist circumference	Interviewer measured	Difference in means	●	●	●●
Diagnosis of other comorbid illnesses		Self-reported	Proportion diagnosed	●		●●
Disability	WHO Disability Assessment Schedule 2.0	Self- reported	Difference in means	●		●●
Quality of chronic illness care received	Patient Assessment of Care for Chronic Conditions (PACIC)	Self-reported	Mean PACIC score	●		●●
Retention in care		Self-reported; clinic records	Proportion in care	●		●●
Health economic outcomes						
Healthcare utilization		Self- reported; linkage with hospitalisation databases	Incidence rate ratio	●		●●
Productivity and economic outcomes		Self- reported		●		●●
Safety measurements						
Hospitalisation		Self- reported; linkage with hospitalisation databases	Proportion hospitalised	●	●	●●
All-cause mortality		Clinic, report, linkage with mortality register	Proportion died	●	●	●●
Suicide		Follow-up of cause of all known deaths with clinic and family interview	Proportion suicides	●	●	●●

^1^● data measured

^2^●● time when endpoint for outcome will be reported

**Table 5 Tab5:** Defining, monitoring and reporting of harm

Type of harm	Source and method of identification	Action(s) to mitigate harm to specific participants	Reporting frequency and to whom
*Adverse Events*			
Positive response to ninth item of the PHQ-9: “Thoughts that you would be better off dead or of hurting yourself in some way”	Participant interviews (baseline, 6-month follow-up, 12-month follow-up)Flag within electronic questionnaire prompting interviewer to act	Repeat question to reduce telescoping-type reporting errorsIf ≥ 8 days in last 2 weeks, immediate referral to clinic staffIf between 1 and 7 days, then written educational material given	6 monthly report to DSMB6 monthly to IRB (with DSMB letter of recommendation)

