Patient recruitment occurred independently of clinical care or participation in the group psychosocial intervention for depression. We adopted a pragmatic approach, enrolling all patients who met the eligibility criteria regardless of exposure to the intervention, recognising that the detection of mental disorders and linkages to care are pressing challenges for integration of mental health services into primary care and that failure to account for this in the design of the trial would limit the generalisability of its findings to real-world primary care settings. Patient participant recruitment started approximately 2 months after the training of nurses and counsellors in the intervention clinics. Trained fieldworkers invited, screened and enrolled patient participants in the trial using a three-stage process as outlined in Additional file 4. First, trained fieldwork recruiters explained the study to patients in the waiting room, inviting those attending for chronic care services to come forward for more information if they were interested. Depression, HIV or ART were not be mentioned during this general information sharing so as not to single out those who wished to participate. The recruiter completed a brief verbal screen of patients who came forward to establish whether or not they were on ART and whether they planned to stay in the study area for the duration of the following year; this was done on a one-to-one basis. Eligible patients were then walked across to a fieldwork interviewer based in a private section of the clinic where the emotional content of the PHQ-9 instrument was explained and opt out consent sought before proceeding with the full screen. We then sought formal consent from patients who screened positive using the PHQ-9. This covered permission to be interviewed at enrolment, at the two subsequent time points, 6 and 12 months later, determination of the participant’s viral load at enrolment and 12 months later, permission to review their clinical folders and hospital records to assess quality of care provided and healthcare utilisation, and to send reminders and confirmation of follow-up interviews by text message and phone calls. We requested participants to supply their national identity numbers to permit linkage with the national population register, which records more than 90% of all deaths in South Africa. We only collected patient identifiers once written informed consent was provided (Additional file 5). The recruitment process for the PRIME and CobALT trials was conducted as a combined process in the [name] district and patient recruitment continued until the target of 50 patients per clinic was met for both trials. We invited patients who were on both ART and antihypertensive medications, and who qualified for enrolment in the trial, to participate in both studies and complete two sets of consent forms. Fieldwork interviewers conduct interviews in one of the three local languages (Setswana, English, Afrikaans), chosen by the participant (see Additional file 6 for the full questionnaire). Fieldwork interviewers collect data using handheld electronic devices, which we have previously used in similar field work data collection exercises in South Africa [80]. We ask participants to return to the clinic for follow-up interviews. We send text reminders in advance of follow-up visits, and contact participants by telephone to confirm their appointments. At follow-up, participants undergo an interview to determine the severity of their depressive symptoms, the nature of the care they received at the clinic, including care for depression and HIV, and other healthcare utilisation and economic outcomes. Follow-up viral loads will be drawn from all patients at 12 months.

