A further serious adverse event that is unlikely to be related to the intervention, but which may occur as a result of participation in the data collection component of the trial, is a markedly elevated viral load in the context of pregnancy, placing the foetus at risk of transmission. For this reason, it will be managed as a serious adverse event and reported to the IRB and DSMB within 7 days. We follow-up all viral loads in excess of 1000 copies/mL to see whether or not they appear to be reported during pregnancy and we urgently pursue all missing viral loads in women who report themselves to be pregnant. Once we confirm a high viral load in a pregnant woman, we immediately notify the clinic staff and advise them to recall the women urgently for clinical care and intervention to limit transmission of HIV to the baby.

We report non-serious adverse events to the DSMB 6 monthly. We ask the participants who respond positively to the ninth item of the PHQ-9 “Thoughts that you would be better off dead or of hurting yourself in some way” to confirm their answer and, if they indicate having such thoughts between 1 and 7 days in the last 2 weeks, we provide them with written educational material on suicide prevention. If they confirm having such thoughts for 8 days or more in the past 2 weeks, we immediately refer them to clinic staff for review. This protocol applied to the pre-screening process even for patients who responded positively to the ninth item of the PHQ-9 but were otherwise not eligible for enrolment in the trial. Likewise, we immediately refer participants with a blood pressure of ≥ 180/110 to clinic staff for review of their blood pressure. Once data collection is complete, we will present a summary of adverse events to clinics together with recommendations for further treatment. These adverse events are a PHQ-9 score of ≥ 20, suggestive of severe depression, raised blood pressure at follow-up representing undiagnosed or uncontrolled hypertension, and detectable viral load at follow-up representing possible adherence problems or treatment failure.

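### The item-9 safety rule decides referral by frequency alone, so as described a participant with suicidal intent or a plan on 1 to 7 of 14 days gets written material only

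*Protocol article*

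**What the plan says.** The Patients section, where it explains the few exclusion criteria, says: "We did not exclude participants with active suicidal ideation, but urgently referred them for clinical review in both intervention and control arms". It gives no definition of the term and no threshold.

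The operating rule appears in two places that agree. In Table 5, under Patient-level outcomes, a positive item 9 sets off a device prompt ("Flag within electronic questionnaire prompting interviewer to act"), and the item is then asked again. The section on adverse events and possible harms states the upper branch: "If they confirm having such thoughts for 8 days or more in the past 2 weeks, we immediately refer them to clinic staff". In both places, a confirmed answer of 1 to 7 days leads to written material on suicide prevention. The same rule covers screening: "This protocol applied to the pre-screening process even for patients who responded positively to the ninth item of the PHQ-9", including patients who were otherwise ineligible.

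The repeat question in Table 2 opens "Please could you confirm your answer for this question" and then restates item 9 word for word. Table 5 gives its purpose as reducing reporting error.

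Two supplementary files that bear on this are cited but not available here. Recruitment is described as "using a three-stage process as outlined in Additional file 4", and for the interview the reader is told to "see Additional file 6 for the full questionnaire".

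**The concern.** Item 9 is one question about two things: thinking one would be better off dead, and thinking of hurting oneself. A day count on that item shows how often the thoughts come, not what they are. Someone with passing passive thoughts on ten days is referred, while someone with a formed plan on three days is handed written material.

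The participants have all screened positive for depression, and the protocol itself allows that suicide could be related to a mental health intervention. At stake is whether a person at risk is seen by clinic staff on the day. The trial's estimates are not at stake.

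**Working it through.** No formula applies to the rule itself, so the check sets the relevant texts side by side.

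**1. Response bands (Table 2) against actions (Table 5 and the adverse-events section)**

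| Confirmed item-9 answer | Score | Action | Intent or plan asked, as described? |
|---|---|---|---|
| 0 days | 0 | none | no |
| 1–7 days | 1 | written material | no |
| 8–11 days | 2 | immediate referral | no |
| 12–14 days | 3 | immediate referral | no |

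The two upper bands reach clinic staff, so the gap is confined to the band scored 1. That band runs up to 7/14 = 50% of days.

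**2. Can the interview separate intent from passive thoughts?** Item 9 cannot, because it joins the two. The repeat question cannot either, because it uses the same words and asks for the same day count. The article describes no other fieldworker question on the matter.

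**3. Is there another route to staff for the 1–7 day band?** Table 3 lists assessing suicide intent as a topic in the supplementary training of nurses in intervention clinics. Basic PC101 training in both arms covers suicidal thinking. Neither is triggered by a 1–7 day answer, because under the described rule that answer does not send the participant to a nurse.

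**4. Does the Patients section conflict with the rule?** There are two readings. If active suicidal ideation there means the band of 8 or more days, the three texts fit together. If it carries a clinical meaning that includes intent or a plan, the sentence promises more than the rule delivers. The article does not define the term, so it cannot settle which is meant.

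**5. Is there still time to act?** Bojanala recruitment began in July 2016 (Trial design), fieldwork was to end in December 2017 (Table 1), and Bojanala follow-up is described as in progress (Trial status). Assuming that end date held and interviews were on time:

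- First 6-month interview: July 2016 + 6 months = January 2017.
- First 12-month interview: July 2016 + 12 months = July 2017.
- Last enrolment: December 2017 − 12 months = December 2016.
- Last 6-month interview: December 2016 + 6 months = June 2017.

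The 6-month window is therefore about January to June 2017, and the 12-month window about July to December 2017. The article does not say which wave was under way.

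**6. Number affected.** The article gives neither the distribution of item-9 answers nor the number of interviews remaining, so no count can be derived.

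**The case against.** The strongest reply is that the document contains no error. The sentence in the Patients section is a summary whose purpose is to say that suicidality was not a ground for exclusion. The exact rule is given twice, consistently, and equating active ideation with intent or a plan is a definition brought in from outside. This stands as far as contradiction goes: a reader might infer that the article contradicts itself, but an undefined term cannot prove that.

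Second, the unseen recruitment and questionnaire files may already contain a risk question. This also stands, and it limits the point to what the article describes. A reader who infers that the trial had no intent assessment at all goes further than the documents allow. The point nevertheless concerns a rule that the article states, with threshold and action, and not merely a detail left out.

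Third, there are other safeguards. Any positive item 9 counts as an adverse event and goes to the DSMB and the IRB every six months. Nurses in both arms receive basic training that touches on suicidal thinking. Nothing forbids a fieldworker from referring someone who volunteers a plan. All of this is true, so it would be wrong to say that control clinics were untrained on the subject or that answers of 1 to 7 days went unmonitored. But aggregate reporting is not same-day care, and the described rule neither sends the 1–7 day responder to those nurses nor asks for the disclosure.

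Fourth, a change in mid-trial makes procedures differ between districts for an unknown benefit. That is a fair cost and is weighed under the fix.

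**Conclusion.** The point holds in limited form. As the article describes it, the item-9 rule turns on frequency alone and gives a participant with intent or a plan on 1 to 7 of 14 days no route to same-day review. This is a minor safety weakness affecting one response category in both arms. It has no effect on sample size, power or the primary analysis.

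The conclusion assumes that the supplementary files add no intent question. It does not show that the Patients section contradicts Table 5, nor that any participant came to harm or was in fact missed. What can be said of the Patients section is that its sentence is looser than the rule and should state the rule that was used.

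**What to change.** For interviews still to be done, in both arms, add one yes/no device question after the PHQ-9 is complete, shown only when the confirmed item-9 answer is 1 to 7 days. It should ask whether the participant currently has thoughts of acting on this, or a plan. Yes or a refusal triggers the same immediate referral as 8 or more days; no leads to written material as now. The 8-day threshold stays. Enter the step and its start date in the item-9 row of Table 5, or, if either supplementary file already contains such a step, cite it there instead. In the Patients section, state the rule applied up to then and refer to Table 5.

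The costs are an ethics notification, a fieldworker briefing and some extra referrals in both arms, where mental health staff are scarce. The likely number is small but unknown. Interviews take place at the clinic and the device already flags item 9, so little new machinery is needed.

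The procedure would differ from the completed district (20 clinics, 1000 patients). Randomisation strata lie within districts, so the arms compared within a stratum would still follow the same rule. The question comes after the PHQ-9, so that interview's score is unchanged. Research viral loads are taken "at baseline and at the 12-month follow-up interview", so a referral made at the 12-month visit should alter neither co-primary outcome. If 6-month interviews remain, the extra referrals would come before the 12-month viral load in both arms and could affect it slightly.

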### Interventions

#### Control arm

The integrated chronic care programme implemented by the Department of Health (described above) forms the control comparison and was implemented in both intervention and control clinics prior to the introduction of the study intervention. At facility level, the main interventions were the reorganisation of chronic care services and training of clinic staff in PC101. Appointment systems and waiting rooms for communicable disease services (HIV, tuberculosis once the intensive phase of treatment has been completed) have been integrated with services catering for NCDs and mental health, resulting in a single chronic care service aimed at reducing fragmentation and promoting integrated care [35]. Nurses in the control facilities are able to refer patients identified as having depression to primary healthcare (PHC) doctors for the initiation of antidepressants (as they are not authorised to prescribe antidepressant medications in South Africa) as well as to mental health specialists, who are limited in number. Limited specialist psychological and psychiatric care is also available at the district hospital.

#### Intervention arm

In the intervention clinics, we supplemented the training of PHC nurse clinicians in the 12 PC101 sessions with clinical communication skills and four additional mental health sessions to strengthen identification and management of depression (see Additional file 3 of web-based supplementary material for examples of PC101 guides). We trained facility trainers in the intervention facilities to deliver this supplementary training material. We did not expose facility-based trainers in the control facilities to this supplementary training. In addition, we strengthened referral pathways for treatment and counselling (see collaborative care model depicted in Fig. 4). For treatment, we provided supplementary training of PHC doctors in mental healthcare. For counselling, we introduced lay behavioural health counsellors into the intervention clinics with structured supervision from district-based psychologists. The initial and long-term intention was to capacitate and diversify the role of existing facility-based lay HIV counsellors to include limited and structured counselling for service users with mild depressive symptoms, so as to ensure sustainability of the service. However, during the formative phase it became apparent that there were a number of scope of practice issues that needed to be addressed at a policy level before this was feasible [42]. So as not to delay the trial, the behavioural health counsellors were thus sponsored from study funds for the duration of the trial. In parallel, in order to optimize future sustainability of the intervention (should it be shown to be effective), the study investigators are engaged in a number of advocacy efforts with policy-makers to diversify the scope of practice of the existing lay HIV counsellors. A comparison of the training provided in the control and intervention clinics is contained in Table 3.

**Fig. 4 Fig4:**
[figure not shown]
Collaborative care package for depression

**Table 3 Tab3:** Comparison of training provided to control and intervention clinics

Provider	Role	Training	Content of training	Method and timeframe
Control and intervention facilities				
PHC nurses	Identifies, provides brief interventions and refers	Basic onsite PC101 training	Case scenarios used for training in the identification and management of common chronic diseases, including communicable diseases, NCDs (including hypertension), women’s health and mental health. Mental health components draw on the WHO’s mhGAP guidelines [91] and adopt a syndromic approach to mental health symptoms (such as stress, insomnia, suicidal thinking) with diagnostic algorithms and treatment checklists for depression	(1) PC101 Master Trainers train Facility Trainers who train PHC nurses at the facilities(2) Twelve weekly sessions over 12 weeks at facilities (two of which are on mental disorders)(3) Training uses case scenario material of patients with chronic conditions, including comorbid conditions
Intervention facilities				
PHC nurses	Identifies, provides brief interventions and refers	Orientation and clinical communication skills training	(1) Overview of the system changes being made by the DoH in South Africa to accommodate the demands of integrated chronic care; their role as case managers within the collaborative care model for depression(2) Orientation to patient-centred care and clinical communication skills necessary to implement patient-centred care(3) Skills to manage patient emotions within the consultation; self-care including how to cope with their own emotions and burn-out(4) Motivational interviewing skills to promote patient self-management	Four 2-h interactive workshops at PHC facilities/regional training centre
		PC101 supplementary training in mental health	(1) Detection of depression and anxiety, psychoeducation and referral to counsellors and/or doctor for consideration of psychotropic medication in the case of moderate severe depression(2) Detection of risky alcohol use and brief intervention for harmful/hazardous drinking and for detoxification and referral to specialists rehabilitation programmes for dependency as per the mhGAP guidelines [91] (3) Assessment of suicide intent (4) Patient review after 8 weeks to assess response to treatment and onward referral for specialist care as indicated by the mhGAP evidence-based guidelines for LMICs [91], if necessary following a treatment-to-target approach as contained in the collaborative care model (Fig. 4); treatment to target involves tracking a patient’s symptom severity and adjusting or intensifying treatment should patients not show an improvement in symptoms following initial treatment.	(1) PC101 Master Trainers train Facility Trainers (2 day workshop) who train PHC nurses at the facilities(2) Three weekly sessions over 3 weeks at facilities, with an additional follow-up session 1 month later(3) Training uses case scenario material of chronic patients with comorbid mental disorders
PHC doctors	Diagnoses, initiates and monitors response to psychotropic medication	Orientation and training in mhGAP/PC101	(1) Orientation to the importance of treating comorbid depression (2) Training in mhGAP guidelines(3) Follow-up using case studies of patients	Three 1-day workshops spread over 6 months
Behavioural health counsellors	Provides evidence-based counselling	Counselling training	(1) Manualised counselling package comprising 8 sessions (delivered individually or in groups) (2) Session 1: Psycho-education session on depression; the last session is a closure session; Sessions 2–7 draw on problem solving and cognitive behavioural techniques, including behavioural activation to address the common triggers of depression and anxiety which, in this population, include poverty, interpersonal conflict, social isolation and avoidance, grief and loss, and stigma that emerged from qualitative interviews held with service users with during the formative phase of the PRIME project in South Africa in two provinces [92]; a prototype had been field tested in KwaZulu-Natal and positive results demonstrated in an individually randomised pilot trial [43]; adherence session provides information on the chronic condition(s) and chronic medication(s) the patients may have as well as helping patients with adherence difficulties (3) While developed to treat depression, the intervention has been found to promote improvements in global psychological functioning as well [43], thus having the potential for trans-diagnostic effects, in line with evidence that diagnosis-specific cognitive behavioural therapy has beneficial effects on untargeted comorbid emotional disorders [43]	One week of off-site training; one week of peer-to-peer mentoring; in vivo supervision by a psychologist of each session; weekly follow-up group supervisory sessions, augmented where possible by weekly individual supervision sessions
Specialists(Psychologist/psychiatrist)	Training, supervision of counsellors	Orientation to task sharing	Psychologists (including interns and community service psychologists) orientated to their roles	Once-off workshops

*DoH* Department of Health, *LMICs* low- and middle-income countries, *mhGAP* WHO Mental Health Gap Action Programme, *NCDs* non-communicable diseases, *PC101* Primary Care 101, *PHC* primary healthcare

